#### 2.9.2. Meningococcal Carriage Power Calculations and Impact on Disease

Assuming an overall carriage prevalence at baseline of 6.8% (B Part of it study, unpublished data), a sample size of 5239 is required in order to have 80% power to detect a 20% reduction at 12 months (alpha = 0.05, two-tailed test) or 7011 participants to have 90% power. We will recruit at least 5239 and up to 7011 participants during the study. This calculation incorporates a correlation between the baseline and 12-month measures of 0.25 (‘B Part of It’ study) and 30% loss to follow-up.

### 2.10. Statistical Analyses

All analyses will be performed according to a pre-specified statistical analysis plan using Stata version 15.

## 3. Primary Objectives

### 3.1. Evaluation of the Effectiveness of 4CMenB Vaccine against Gonorrhoea in 15 to 19 Year Olds

The primary analysis on vaccine effectiveness (VE) will be performed using a case–control method using controls from the sexually transmitted infections (STI) notification database for chlamydia. A case will be defined as any laboratory confirmed case of gonorrhoea among 15–19-year-olds notified to the CDC. For each case, up to four controls will be randomly sampled from a de-identified dataset of individual records extracted from the Chlamydia notification database of the CDC. Although increasing the number of controls per case increases statistical power, beyond a ratio of four controls per case only small improvements in power are expected [24,25]. A secondary case–control analysis will be performed using controls from the Australian Immunisation register (AIR). For each case, up to 20 controls will be randomly sampled from a de-identified dataset of individual records extracted from the AIR, following restriction of the database to the NT to ensure sampling from the same population. A previous similar study on assessing the effectiveness of the varicella vaccine in Australia has shown maximum precision using 20 controls per case [26]. Controls from both AIR and STI databases will be matched to cases by date of birth ± 4 weeks. Vaccination status of controls will be ascertained from the AIR after selection and vaccination considered valid if received ≥3 months before the date of laboratory confirmation of gonorrhoea in the matched case. This method of control ascertainment has been used previously to assess VE of *Haemophilus influenzae* serotype B, pertussis, varicella and measles vaccines in Australia [26]. Conditional logistic regression models will be generated in Stata to estimate VE.

VE will also be estimated using the screening method for 15–19-year-olds with laboratory-confirmed gonorrhoea within 3 months of receiving two doses of the 4CMenB vaccine. The comparator group will include all 15–19-year-olds in the NT. Using the screening method, VE will be estimated as $1-\frac{PCV(1-PCV)}{PPV(1-PPV)}$ where *PCV* is the proportion of vaccinated MenB cases and *PPV* is the vaccine coverage in the age group being analysed [27]. Vaccine coverage data for each age group will be obtained from the AIR.

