## 2. Materials and Methods

Exclusion criteria include anaphylaxis following any component of the Bexsero^®^ vaccine, previous receipt of the MenB vaccine, Bexsero^®^ (previous receipt of MenNZB^TM^ is allowed), known pregnancy, clinical conditions representing a contraindication to intramuscular vaccination and venepuncture. A temporary exclusion of a 14-day interval between receipt of study vaccine and COVID-19 vaccines applies. Eligible 14–19-year-olds can participate in the study via schools or via government and non-government immunisation clinics including Aboriginal Community Controlled Health Organisations (ACCHO). The 14–19-year-old age group is selected to enable vaccination prior to rapid carriage and STI acquisition. Conducting the study in schools provides an opportunity to use the existing school immunization program and infrastructure in a closed accessible environment with potential for the highest rates of participation. The objectives and outcome measures are detailed in Table 1.

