#### 2.9.1. Gonorrhoea Infection Power Calculations

Case–control study: To assess the vaccine effectiveness of 4CMenB on gonorrhoea, assuming 1350 cases of gonorrhoea among 15–19-year-olds in the NT (Australian Bureau of Statistics) over a three year period (i.e., 450 per annum), a ratio of 3 matched controls to 1 case and assuming 50% of the eligible control population vaccinated with a correlation of 0.1, the study has at least 90% power at alpha = 0.05 to detect vaccine effectiveness of at least 20% (i.e., OR = 0.8 or less) and allowing for correlation between cases and controls on basis of 0.2. With this estimated number of cases and controls, the study is adequately powered even if 40% of the eligible population is vaccinated.

Interrupted time series study: A power simulation study that assumed three years of monthly observations post-implementation in each of the vaccinated and unvaccinated groups, constant gonorrhoea counts over time in the unvaccinated group (i.e., ~450/12 = 37.5 cases per month, so µ = 3.62), and a Poisson distribution of counts was conducted. Using the method of Feiveson with 1000 runs, the power to detect a coefficient of −0.008 in the vaccinated group as significant is 0.84 (alpha = 0.05, two-tailed test). This equates to a 9.6% reduction in cases in the vaccinated group relative to unvaccinated group (from 450 to 407 cases p.a.), assuming the two groups are of equal size.

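### Chlamydia controls in the primary VE analysis are matched on birth date but not on notification date, so sexual activity and contact with care at the index date are controlled less well than intended

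*Protocol article*

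**What the plan says.** The relevant rules are in Section 3.1 of the protocol article.

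- **Cases:** "any laboratory confirmed case of gonorrhoea among 15–19-year-olds notified to the CDC".
- **Primary controls, per case:** "up to four controls will be randomly sampled from a de-identified dataset of individual records extracted from the Chlamydia notification database of the CDC".
- **Matching, both control sources:** "Controls from both AIR and STI databases will be matched to cases by date of birth ± 4 weeks". No other matching variable is named.
- **Exposure in controls:** taken from the immunisation register (AIR) after selection, with "vaccination considered valid if received ≥3 months before the date of laboratory confirmation of gonorrhoea in the matched case".

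The clock for exposure is therefore the case's date. The control's chlamydia date is used neither to select the control nor to read vaccination.

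Section 2.8 lists differences in care seeking for STI treatment and for vaccination, and variation in screening, among the potential biases. It relies on two control groups and the screening method to triangulate.

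**The concern.** A chlamydia notification shows that a person was sexually active and being tested at about that time. This is the reason to prefer such controls to register controls when the outcome is gonorrhoea. The information is dated, and the matching rule discards the date.

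AIR controls have no event date, so birth-date matching with the case's index date suits them. Section 3.1 supports the method by its earlier use for other childhood and adolescent vaccine-preventable diseases. For chlamydia controls the same rule leaves open when the qualifying event happened. Because birth dates are matched, a gap in calendar time is also a gap in age at the event. A control notified well after the case was selected on a future event and may not have been sexually active or tested at the index date. A control notified well before may have had a clinic contact that the case lacked, and Section 2 names clinics as one route to the vaccine.

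At stake is how well the primary comparison controls for sexual activity and contact with care at the moment vaccination is read. The other two analyses cannot make this good, since neither AIR controls nor the screening comparator is restricted to tested, sexually active young people.

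**Working it through.** **1. Inputs.** Section 3.1 gives birth date ± 4 weeks as the only matching variable and an age range of 15–19. Section 2.9.1 gives the case count ("assuming 1350 cases of gonorrhoea among 15–19-year-olds in the NT"), a three-year period at 450 a year, and "a ratio of 3 matched controls to 1 case". The article does not state the extraction period of the chlamydia data or the number of chlamydia notifications.

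**2. The plan's own figure.** The document gives no figure for the time between case and control notifications. The nearest stated figure is power of at least 90%. With 50% of controls vaccinated and OR 0.8, the vaccinated share in cases is 0.5 × 0.8 / (1 − 0.5 × 0.2) = 0.444. Dupont's matched case-control formula (1350 cases, 3 controls each, two-sided alpha 0.05) gives:

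| Exposure correlation | Power |
|---|---|
| 0 | 94.3% |
| 0.1 | 93.1% |
| 0.2 | 91.4% |

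The stated power reproduces. It concerns precision and does not bear on who is eligible as a control.

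**3. Gap with no age limit on the control's notification.** Take case and control dates as independent and uniform over T = 36 months.

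- Mean gap = T/3 = 36/3 = 12.0 months.
- Share of pairs more than g months apart = (1 − g/36)².
  - g = 3: (33/36)² = 0.84
  - g = 6: (30/36)² = 0.69
  - g = 12: (24/36)² = 0.44

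**4. Gap when the control must also be 15–19 at notification.** The eligible period is then shorter for some birth dates. This was simulated with 400,000 pairs: case date uniform over three years, case age uniform from 15 to under 20, same birth date, control date uniform over the eligible part of the window. The mean gap is 9.6 months (median 7.7). Of the pairs, 77% are more than 3 months apart, 59% more than 6 and 33% more than 12. If notifications rise with age, the mean is 9.3 months.

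**5. Other assumptions (control aged 15–19).**

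| Assumption | Mean gap, months |
|---|---|
| Two-year window | 6.9 |
| Four-year window | 11.7 |
| Extract also covers the six pre-vaccine years | 15.0 |

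**6. What is and is not aligned.** Within a set, birth dates agree to 4 weeks and vaccination is read at one date. Case and control therefore have the same age and the same stage of roll-out at that date. Being sexually active and in contact with care is tied to that date for the case but not for the control.

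**7. Effect of a date window.** With control dates uniform within ± 3 months of the case, the mean gap is 3/2 = 1.5 months. For feasibility, assume 450 to 900 chlamydia notifications a year at ages 15–19 (an assumption). Half a year of notifications, times the fraction of a five-year birth range covered by 8 weeks (8/260), gives 225 × 0.031 ≈ 7 to 450 × 0.031 ≈ 14 candidates per case. Power in step 2 is unchanged while about three controls per case remain.

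**The case against.** The strongest reply is that exposure is already aligned: same age, same calendar date, same opportunity for vaccination within each set. That stands. It disposes of one tempting inference, that coverage rising through the roll-out distorts the comparison. It does not, because both members of a set are read at the same point of the roll-out.

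A reader might also infer that the VE is biased upward by a calculable amount, because a control notified earlier had an extra chance to be vaccinated. The document does not support this. With uniform dates and no age limit, 0.5 × (33/36)² = 42% of controls are notified more than 3 months before the case, but another 42% more than 3 months after, and their effect may run the other way. Cases too may have had earlier clinic contacts. Any uplift in vaccination from such a contact would have to be invented.

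Nor does Section 2 say that sexual exposure changes rapidly throughout the 15–19 band. It says only that "The 14–19-year-old age group is selected to enable vaccination prior to rapid carriage and STI acquisition". Extreme pairs are uncommon: a control notified more than two years after the case makes up 0.5 × (12/36)² ≈ 6% of pairs without an age limit.

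Section 2.8 does acknowledge the care-seeking bias and plans triangulation and adjustment for background rates. This is fair, but none of it ties a control to the case's date.

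Finally, the article condenses a full protocol, and an analysis plan may add a date window. That is possible, but the article states the matching rule outright for both control sources, and the rule as stated contains none.

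**Conclusion.** The point holds as a weakness in a stated design rule. Under birth-date matching alone, the control's chlamydia notification would lie on average about 10 to 12 months from the index date. This assumes uniform notifications over the protocol's three-year window; about 7 to 15 months covers the other assumptions tried. The control group therefore controls sexual activity and contact with care at the index date only in part, and the primary VE can carry residual confounding.

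It would go too far to say that the VE is biased, or that chlamydia controls fail altogether. Neither the direction nor the size of any bias can be derived from the document. The change is nevertheless worth making before controls are drawn, because this is the primary analysis and the only one restricted to tested, sexually active young people.

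**What to change.** For the chlamydia analysis in Section 3.1, add a second selection condition: the control's notification or specimen date must lie close to the case's, for example within ± 3 months, in addition to birth date ± 4 weeks. Where too few controls are found, widen the birth-date window before the notification-date window. State the extraction period of the chlamydia dataset. Leave the AIR controls as they are.

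The cost is one more condition on a date that a notification record should already carry. Some cases will have fewer than four controls or a wider birth-date window. How many depends on chlamydia notification counts, which the article does not give and which should be checked before the window is fixed.

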Emerging evidence suggests that 4CMenB may protect against gonorrhoea, a sexually transmissible infection (STI) which is identified by the World health Organisation as a public health priority. An estimated 106 million cases of gonorrhoea are diagnosed worldwide each year with the number increasing in recent years [9]. Gonococcal infections commonly present as urethritis in males and cervicitis in females, but mucosal infections of rectum, pharynx and eye frequently occur [10,11,12]. In addition, gonococcal infections can lead to pelvic inflammatory disease, adverse pregnancy outcomes, infertility and neonatal complications. In Australia, gonorrhoea notifications increased by 80% over a 5-year period from 2013 to 2017 (from 65.5 to 118 per 100,000) [13]. The Northern Territory (NT) has the highest rate of gonorrhoea notifications in Australia with 686.6 per 100,000 reported in 2017 [14]. The gonorrhoea notification rate in the Aboriginal and Torres Strait Islander population was 6.6 times higher than the non-Indigenous population in 2017 (627.5 per 100,000 versus 95.6 per 100,000) [13]. A recent study on potential disseminated gonococcal infection between January 2010 and September 2018 reported 106 cases in the Top End of the NT. Of these, 94 (88.7%) were among Indigenous Australians and the highest incidence was in the 15–19 year old age group [15]. Variations exist across regions within the NT, which is divided into two major areas; the Top End which covers 516,945 square kilometres and a population of approximately 250,000 and Central Australia, which covers 830,220 square kilometres and a population of approximately 41,000. The Central Australian region communities have much higher notification rates than the Top End communities.

The effectiveness of antibiotics for gonorrhoea has been compromised due to emerging resistance to broad-spectrum Cephalosporins, and development of an effective gonorrhoea vaccine has been challenging. However, surveillance reports from Cuba, New Zealand and Canada showed a decline in gonorrhoea incidence following vaccination against *N. meningitidis* [10,11,12,16]. A recent transmission-dynamic model showed that a vaccine conferring 31% protection (as estimated for the MeNZB) for 2–4 years could reduce the incidence of gonorrhoea by 45% by 2030 [17].

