### 2.8. Data and Statistical Analysis Plan

Basic demographic data and risk factors for meningococcal disease (from the questionnaire), laboratory results and vaccination data will be entered into the study database. IMD and gonorrhoea rates will be obtained from routine surveillance data from the CDC, NT. For the case–control and screening method analyses, data custodians from AIR and CDC NT will link participant records and assign unique study IDs prior to sending data to the study team. No identifying information will be stored in the main study database. Infection rates for IMD and gonorrhoea for various demographic subgroups will be estimated from CDC NT surveillance data, and a many-to-one merge will be used to link background rates to individual records, so as to adjust for these rates in the subsequent analyses.

There are some limitations for observational studies with potential for bias and confounding. Some of the potential sources of bias identified include, any changes to the current practice of notifications over the study period, differences in case ascertainment due to variation in extent of screening and contact tracing, differences in healthcare seeking behaviour for STI treatment and vaccination, extent of other STI prevention/health promotion programs offered in the region, missing data, misclassification of the outcome, differences in lab diagnostics and those lost to follow up during the study period.

To partly mitigate the effects of some of the potential biases, different study designs will be utilized in the investigation of the research hypotheses. This approach will aid in triangulation of findings and strengthen the conclusions that will be drawn from the study [23]. Since there is considerable debate about the circumstances under which causality can be tested or assumed, we will use two different approaches with differing and unrelated key sources of potential biases in assessing vaccine effectiveness. The two are the screening approach and the case–control approach. In the screening approach, results are compared between different populations in different contexts (cross-context comparisons). In the case–control approach, two different control groups will be used, namely controls from the STI notification (Chlamydia) database and the Australian Immunisation register (AIR). These approaches will not give the same estimates of the causal effect unless all analyses are unbiased.

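### Gonorrhoea VE is matched or compared on age alone; the planned background-rate adjustment is not carried into section 3.1, cannot enter the screening formula, and agreement of screening with AIR controls would not show absence of bias

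*Protocol article*

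**What the plan says.** Section 3.1 sets out three VE analyses: the primary case–control analysis with chlamydia-notification controls, a secondary one with controls from the Australian Immunisation Register (AIR), and the screening method.

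- **Matching:** "Controls from both AIR and STI databases will be matched to cases by date of birth", with a window of 4 weeks either side. AIR controls are drawn "following restriction of the database to the NT to ensure sampling from the same population".
- **Model:** "Conditional logistic regression models will be generated in Stata to estimate VE". Section 3.1 names no covariates. Section 3.2, on carriage, names gender, ethnicity and remoteness among others.
- **Screening:** "The comparator group will include all 15–19-year-olds in the NT". Coverage is taken from the AIR by age group.
- **Risk differences:** the Introduction states "The gonorrhoea notification rate in the Aboriginal and Torres Strait Islander population was 6.6 times higher than the non-Indigenous population in 2017" and says that notification rates in Central Australian communities are well above those in the Top End.
- **Planned adjustment:** section 2.8 will estimate infection rates for unnamed demographic subgroups from surveillance data, and then "a many-to-one merge will be used to link background rates to individual records, so as to adjust for these rates in the subsequent analyses".
- **Triangulation:** section 2.8 describes the screening and case–control approaches as having unrelated sources of bias, and concludes: "These approaches will not give the same estimates of the causal effect unless all analyses are unbiased".
- **Stratified estimates:** Table 1, objectives 4 and 5, adds gonorrhoea estimates by gender and by location as secondary objectives. Aboriginal status is not among the strata.

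**The concern.** Aboriginal status and region are strong determinants of gonorrhoea in the article's own figures. If vaccine uptake through schools and clinics also differs by these factors, they confound VE, and matching on date of birth does nothing about it. The article gives expected participation only overall (40–50%), so the size and direction of any uptake gap are unknown.

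Two things are at stake. First, the study is powered for a VE of 20%, and confounding of similar size is possible in the screening and AIR analyses if they are run as section 3.1 describes them. Second, section 2.8 tells the reader to take agreement between approaches as evidence that all are unbiased. Screening and AIR controls use the same cases, the same reference population and the same register, so they would tend to agree even when both are confounded.

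**Working it through.** **Inputs from the article.** Aboriginal share of the eligible population: 5621/14,077 = 39.9%, used as 0.40. Rate ratio by Aboriginal status: 627.5/95.6 = 6.56, stated as 6.6. Benchmark effect: VE 20% (OR 0.8) with at least 90% power, for 1350 cases, 3 controls per case and 50% control coverage.

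**The plan's own figure.** Dupont's matched case–control formula (two-sided alpha 0.05) gives power of 93.1% with correlation 0.1 and 91.4% with correlation 0.2. The stated power reproduces, so 20% is a fair yardstick.

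**Assumptions.** True VE is 0, coverage differs by Aboriginal status only, and the screening formula takes its standard odds form, VE = 1 − [PCV/(1 − PCV)] / [PPV/(1 − PPV)]. The coverage gaps are assumed; the article gives none.

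**Step 1, case mix.** Aboriginal share of cases = 0.4 × 6.6 / (0.4 × 6.6 + 0.6) = 2.64/3.24 = 0.815.

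**Step 2, screening and unadjusted AIR controls.** AIR controls sample the coverage that PPV measures, so one calculation serves both. With coverage 35% Aboriginal and 50% other:
- PPV = 0.4 × 0.35 + 0.6 × 0.50 = 0.440
- PCV = 0.815 × 0.35 + 0.185 × 0.50 = 0.378
- VE = 1 − (0.378/0.622)/(0.440/0.560) = +22.7%

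With the coverages reversed, PPV = 0.410, PCV = 0.472 and VE = −28.8%.

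| Coverage gap (higher group 50%) | Aboriginal coverage lower | Aboriginal coverage higher |
|---|---|---|
| 0 points | 0% | 0% |
| 5 points | +8.0% | −8.7% |
| 10 points | +15.5% | −18.2% |
| 15 points | +22.7% | −28.8% |

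At a 15-point gap, a rate ratio of 2 gives +10%/−11% and a rate ratio of 10 gives +25%/−33%.

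**Step 3, primary analysis.** With chlamydia controls the reference coverage is that of chlamydia cases. For a chlamydia rate ratio of 2 (assumed), the Aboriginal share of controls is 0.8/1.4 = 0.571, control coverage is 0.571 × 0.35 + 0.429 × 0.50 = 0.414, and VE = 1 − (0.378/0.622)/(0.414/0.586) = +14%; reversed, −16%. At a ratio of 4 it is +5%/−5%, and at 6.6 it is 0%.

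**Step 4, does the background-rate adjustment help?**
- *Conditional logistic model, general-population controls.* In simulation (100,000 matched sets per setting, 4 or 20 controls per case, 15-point gap), unadjusted VE was +21.7% to +23.6%, or −27.2% to −28.6% with coverages reversed. With the log subgroup rate as a covariate it was −1.5% to +1.5%, which is zero within simulation error. This requires that the subgroups separate Aboriginal status.
- *Chlamydia controls.* Confounding here runs through the ratio of gonorrhoea to chlamydia. Take two equal strata with the same gonorrhoea rate, a twofold difference in chlamydia rate, and coverage of 35% and 50% (all assumed). The merged rate cannot tell the strata apart. Case coverage is 0.425. Control coverage is 0.45 if the high-chlamydia stratum has the 50% coverage, giving VE 1 − (0.425/0.575)/(0.45/0.55) = +10%. It is 0.40 if that stratum has the 35%, giving −11%.
- *Screening.* The formula uses one PCV and one PPV per age group. An individual-level covariate has nowhere to enter.

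**The case against.** The strongest reply is that adjustment is already planned. Section 2.8 commits to linking subgroup rates to individual records and adjusting for them, Table 1 stratifies by gender and location, section 2.10 refers to a pre-specified analysis plan that is not shown, and a conditional logistic model accepts covariates. This largely stands. A reader might infer that all gonorrhoea VE analyses leave Aboriginal status, region and sex uncontrolled, but the documents do not support that. Silence in section 3.1 does not establish an unadjusted model, and Step 4 shows that the planned adjustment can remove the bias with AIR controls. When Aboriginal status is the only confounder, a two-level rate is as good as an indicator for it, with chlamydia controls too.

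A reader might also carry +23%/−29% over to the primary analysis, or treat it as a forecast. Neither is supported. The coverage split is assumed. The 6.6 is a national figure not restricted by age: the NT overall rate of 686.6 per 100,000 exceeds both rates behind it. The chlamydia-control figures are smaller over the ratios shown.

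Nor would the screening and AIR results be literally identical. The equality needs the odds form and unadjusted analyses; the formula as printed gives +4.6% and −3.0% on the 15-point inputs.

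Three points remain. The adjustment is not carried into section 3.1 and its subgroups are unnamed. It cannot enter the screening method as described. And the triangulation sentence is wrong for one pair of analyses whatever an analysis plan may add on covariates.

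**Conclusion.** The point holds as a need to reconcile sections 2.8 and 3.1 and to change stated rules, not as proof that VE will be confounded. Date of birth is the only stated matching variable and age the only stated coverage stratum, against strong risk differences that the article itself reports.

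If uptake differs by Aboriginal status and nothing is adjusted, the null bias in screening and AIR-control VE is about 8–9% in size for a 5-point gap, 16–18% for 10 points and 23–29% for 15 points, in either direction. It is zero with no gap. In the primary analysis a 15-point gap gives +14%/−16% down to 0% over chlamydia rate ratios of 2 to 6.6. The article gives no chlamydia rates, so the position within or outside that range is unknown. These figures rest on the assumed gaps, the national rate ratio, 40% Aboriginal and the odds form of the screening formula.

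The triangulation sentence is incorrect for screening against AIR controls. They share cases, reference population and confounders, so their agreement is compatible with a common bias.

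**What to change.** 1. Reconcile sections 2.8 and 3.1: name the demographic subgroups and say how the adjustment enters each analysis.
2. Name Aboriginal status, region or remoteness, and sex as matching variables or covariates in every gonorrhoea conditional logistic model. With these in the model, the chlamydia-control analysis does not depend on a gonorrhoea rate as a proxy.
3. Run the screening method by strata of age, sex, Aboriginal status and region with stratum-specific coverage, as a logistic regression of vaccination status among cases with logit(PPV) as offset.
4. If background rates are kept, estimate them from pre-vaccine years only, so that they do not contain the vaccine's effect or draw on the cases being analysed.
5. Replace the triangulation sentence: agreement of screening with AIR controls is not independent corroboration; the informative contrast is chlamydia against AIR controls.

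**Cost:** wording, plus the same variables in the data custodians' extracts for cases, controls and coverage denominators. Sex and location are already needed for objectives 4 and 5. The price is slightly wider intervals and some missing values for Aboriginal status, whose handling should be stated.

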### 4.3. Meningococcal Disease

Evaluation of the vaccine impact and effectiveness of 4CMenB administered to young adults on group B IMD in 14- to 19-year-olds.

Vaccine impact on IMD will be estimated using surveillance data from CDC for laboratory-confirmed IMD cases, comparing six pre-vaccine surveillance years to three post-vaccination years as described above for gonorrhoea. Vaccine effectiveness (VE) will be evaluated using screening and case–control methods as described for gonorrhoea. For the case–control analysis, controls will be selected from AIR (20 controls per case). Controls will be matched to cases by date of birth±4 weeks. Vaccination status of controls will be ascertained from the AIR after selection and vaccination considered valid if received ≥14 days before the date of laboratory confirmation of IMD in the matched case.

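### The screening analysis for gonorrhoea states a vaccination window (within 3 months of two doses) opposite to the case–control rule (at least 3 months before confirmation), and it cannot give a valid estimate as written

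*Protocol article*

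**What the plan says.** All of the following is in the protocol article.

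- **Case–control analysis, section 3.1.** Cases carry no vaccination condition: "A case will be defined as any laboratory confirmed case of gonorrhoea among 15–19-year-olds notified to the CDC". For controls, exposure is dated against the matched case, with "vaccination considered valid if received ≥3 months before the date of laboratory confirmation of gonorrhoea in the matched case". No number of doses is given in that rule.
- **Screening analysis, section 3.1.** The analysis is described for 15–19-year-olds with "laboratory-confirmed gonorrhoea within 3 months of receiving two doses of the 4CMenB vaccine". The comparator is broad: "The comparator group will include all 15–19-year-olds in the NT". PCV "is the proportion of vaccinated MenB cases and" PPV is vaccine coverage in the age group analysed, taken from the Australian Immunisation Register (AIR). No time lag is attached to PPV.
- **Meningococcal disease, section 4.3.** The control rule is "vaccination considered valid if received ≥14 days before the date of laboratory confirmation of IMD in the matched case", which runs in the same direction as the gonorrhoea case–control rule. The same section says "Vaccine effectiveness (VE) will be evaluated using screening and case–control methods as described for gonorrhoea".
- **Role of the analysis.** Table 1 lists screening under the other analyses for primary objective 1. The primary analysis is the case–control comparison with chlamydia controls. Section 2.8 names screening and case–control as the two approaches to be set against each other in judging bias.

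**The concern.** For one vaccine and one endpoint, one paragraph asks for at least 3 months between vaccination and confirmation and the next asks for no more than 3 months. Nothing in the article explains the difference.

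The screening method is sensitive to this because it compares two proportions that must describe the same exposure. If PCV is limited to a short window after dose two while PPV is plain coverage, the comparison is no longer of like with like and the estimate moves for reasons unrelated to protection.

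The consequence goes beyond one supporting estimate. Section 2.8 argues that the approaches will agree only if all are unbiased. Opposite windows would make them disagree by construction, and the gap could be read as evidence about confounding. Section 4.6 plans cost-effectiveness ratios under the alternative effectiveness methods, so a faulty screening estimate could reach those too. Because section 4.3 refers back to the gonorrhoea methods, the wording could also carry over to meningococcal disease.

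**Working it through.** The article gives no expected effectiveness or power for the screening analysis, so there is no figure to reproduce. The check asks what the stated window would return.

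**Inputs from the article.** The window is 3 months (section 3.1). Coverage is 50%, with 40% as the alternative (section 2.9.1). The case-accrual period is "over a three year period (i.e., 450 per annum" (section 2.9.1), used here as 36 months.

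**Assumptions that are not in the article.** Incidence is constant, everyone vaccinated is followed for the same T months after dose two, and there is no protection in the first 3 months. T of 24 and 12 months is shown as well as 36.

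**Formulas.**
- Standard: VE = 1 − [PCV/(1 − PCV)] × [(1 − PPV)/PPV]
- Printed in section 3.1: VE = 1 − PCV(1 − PCV)/[PPV(1 − PPV)]

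**Reading A: the sentence taken literally.** All screening cases have had two doses, so PCV = 1. In the standard formula PCV/(1 − PCV) has a zero denominator, and VE tends to minus infinity as PCV approaches 1. In the printed formula the numerator is 1 × 0 = 0, so VE = 100% at any coverage.

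**Reading B: unvaccinated cases kept, vaccinated cases within 3 months counted, later vaccinated cases dropped.** For a vaccine with no effect, at 50% coverage and T = 36:
- vaccinated cases counted are proportional to 0.5 × 3/36 = 0.0417, and unvaccinated cases to 0.5
- PCV = 0.0417/0.5417 = 0.077
- standard VE = 1 − (0.077/0.923) × (0.5/0.5) = 0.917

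In general PCV/(1 − PCV) = [PPV/(1 − PPV)] × 3/T. Coverage cancels and the standard formula gives VE = 1 − 3/T.

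**Reading C: as B, but later vaccinated cases counted as unvaccinated.** At 50% coverage PCV = 0.5 × 3/T. For T = 36, PCV = 0.0417 and VE = 1 − 0.0417/0.9583 = 0.957.

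Results for a vaccine with no effect, at 50% coverage:

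| T (months) | Vaccinated cases inside window (3/T) | Reading B, standard formula | Reading C, standard formula |
|---|---|---|---|
| 36 | 8.3% | 91.7% | 95.7% |
| 24 | 12.5% | 87.5% | 93.3% |
| 12 | 25% | 75.0% | 85.7% |

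Reading B gives the same value when the true effectiveness from month 3 is 20% or 40%, because the cases in which that protection would show are not used.

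**Sensitivity to the formula.** With the printed formula, Reading B at T = 36 and 50% coverage gives 1 − (0.0769 × 0.9231)/0.25 = about 72%.

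**With the windows aligned.** Count vaccination only from 3 months onward in both PCV and PPV. With a true VE of 20% at 50% coverage, vaccinated cases are proportional to 0.5 × 33 × 0.8 = 13.2 and unvaccinated cases to 0.5 × 33 = 16.5. PCV = 13.2/29.7 = 0.444, and the standard VE = 1 − 13.2/16.5 = 0.20. The assumed value is recovered, and this also holds at 40% coverage.

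**The case against.** The strongest reply is that the sentence is a drafting slip for at least 3 months after vaccination. The literal sentence cannot be executed, since PCV needs unvaccinated cases, and the meningococcal rule in section 4.3 runs the other way. A statistical analysis plan that is not shown may already have it right. This is plausible, but the article does not leave the window open. It states one, and that one conflicts with the paragraph before it. A slip still has to be corrected.

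Three stronger inferences are tempting and are not supported:

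- **That the study will report an effectiveness near 92% for a useless vaccine.** That figure is 1 − 3/T for a chosen T. It needs Reading B, which section 3.1 does not spell out, and the standard formula in place of the printed one. Vaccination spread over 2021–2022 and participants ageing past 19 would make follow-up unequal. The figures show the direction and possible size of the error and do not forecast a result.
- **That infections soon after vaccination should be excluded.** The case–control rule drops no infections. It treats vaccination less than 3 months before confirmation as not valid, and the person remains a case. The rule is also written for controls, and applying it to cases is implied rather than stated.
- **That the primary result is at risk.** Table 1 places screening among the other analyses. The chlamydia-control analysis has its own validity rule and does not use this sentence.

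The form of the printed formula, and its reference to MenB cases in a gonorrhoea section, are separate matters on which this point does not depend.

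**Conclusion.** The contradiction stands. Section 3.1 fixes opposite windows for the same endpoint, and none of the three readings examined makes the screening sentence usable. Taken literally, PCV = 1 and effectiveness is either undefined (standard formula) or 100% (printed formula). With unvaccinated cases restored, PCV and PPV measure different exposures. A null vaccine then shows about 75% to 92% with the standard formula if later vaccinated cases are dropped, and about 86% to 96% at 50% coverage if they are counted as unvaccinated. These ranges assume 12 to 36 months of follow-up after dose two, constant incidence, equal follow-up and no early protection.

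The damage is limited to a supporting analysis under primary objective 1 and to whatever draws on it: the triangulation in section 2.8, the cost-effectiveness work in section 4.6, and possibly the meningococcal screening analysis. It should be corrected before that analysis is run.

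**What to change.** Replace the screening sentence in section 3.1 with a definition that does three things:

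1. Includes all laboratory-confirmed gonorrhoea cases in 15–19-year-olds, vaccinated and unvaccinated.
2. Counts a case as vaccinated only if the qualifying vaccination was received at least 3 months before laboratory confirmation. Infections sooner than that are not counted as vaccinated cases.
3. Takes PPV from the AIR under the same dose and lag definition, so that people vaccinated less than 3 months earlier are handled alike in PCV and PPV.

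The case–control rule should say that it applies to cases as well as controls. The number of doses that makes a vaccination qualifying should be stated once for both methods, since only the screening sentence gives one now. In section 4.3, state that the meningococcal screening analysis uses that section's own 14-day rule rather than inheriting the gonorrhoea window.

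The cost is a few sentences in the protocol and the matching entry in the statistical analysis plan. No new data source is needed. Vaccination status and coverage already come from the AIR, and coverage has only to be extracted by vaccination date with a 3-month lag.
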